#### Assessment of the outcomes

A registration form has been developed to use during the assessment and data collection of outcomes. The form is designed so the teacher can click whether the student answers options 1, 2, 3, or 4. It is the student’s teacher who will carry out all the tests. The teacher must register correct or incorrect responses during the assessment. Only the teacher and the student will be present during the testing, and all test situations will be filmed. Each student will receive an individual follow-up plan that will describe in detail when tests will be carried out and when the intervention will start. Within each phase, 20% of the recorded films will be randomly selected and evaluated by two external raters at item-level across the five primary outcomes. Agreement between the two raters and the teachers will be checked, and in case of agreements below 80%, all the films will be checked.

#### Primary outcomes

Primary outcomes will be assessed 18 times in equidistant time points, every month, across 18 months. All the below described tests were developed by the first and second author. To the best of our knowledge, there are no such available tools in Norwegian to assess this population who uses AAC with demonstrated evidence of validity. They are centered on the following phonological awareness skills domains:Sound blending [score ranging from 0 to 10] measured by adapted tests in line with the reading material “Lesing for alle.” Researcher-designed test. Testing in sound blending involves testing the student’s ability to combine individual sounds into words. The students will see a sheet of paper with four symbols. In the instructions, the target word will be presented by expanding the individual sound in the word. For example, “sss-uuu-nnn.” The students have to listen to the sounds, put the sounds together in their head, and then point to the symbol that belongs to the word. This test consists of 10 tasks. The teacher will make no comments on the accuracy of student’s selections but just comment “good work” for the motivation.

Example of one test task in sound blending:

Wigdit symbols [47].2)Letter-sound correspondence [score ranging from 0 to 25] measured by adapted tests in line with the reading material “Lesing for alle.” Researcher-designed test. Testing in letter-sound correspondence involves testing the student’s ability on the correspondence between the sounds of speech (phonemes) and the written letters that represent speech (graphemes). The instructor asks the student to choose, for example, the letter sound “*a*.” The student must then discriminate between the target sound and three others. This test consists of 25 tasks.3)Phoneme segmentation [score ranging from 0 to 10] measured by test in line with the reading material “Lesing for alle.” Researcher-designed test. Testing in phoneme segmentation tests the student’s ability to segment the first phoneme of the word (e.g., *s* for *sun*). Then, the student must select the symbol for the word that begins with the target phoneme. The student must discriminate between four symbols. The instruction asks the student to find the word that starts with, for example “*a*.” This test consists of 10 tasks.

#### Secondary outcomes

The time frame is as follows: two time points during baseline phase, two during intervention (months 1, 12, and 18). In the same way as described above, we have a lack of evidence in terms of validity in the following tests in Norwegian, and those assessments were specially developed for this population. Part of this study is focused on providing evidence based on other variables [50].Recognition of sight words [score ranging from 0 to 10] measured by adapted tests in line with the reading material “Lesing for alle.” Testing in sight words measures the student’s ability to recognize words learned by sight, i.e., words that are difficult to decode. The student must discriminate between one target sight word and three others. The three other words consists both of other novel sight words, words that start with the same first sound as the target word and words of similar form. This test consists of 10 tasks with consonant–vowel-consonant (CVC), CV, VCVC, CCVC, VCCVC, and VCC words.Decoding [score ranging from 0 to 20] measured by adapted tests in line with the reading material “Lesing for alle.” Testing in decoding tests the student’s ability to (1) recognize the letters in the word, (2) associate each letter with its corresponding sound, (3) hold these sounds in sequence in working memory, (4) blend the sounds to determine the word, (5) retrieve the meaning of the word [51], and, finally, (5) select the symbol that represents the word. The students must discriminate between four symbols, where one symbol represents the target word, and the other three consist of words with the same first sound, novel words, and words with similar forms. This test consists of 20 tasks with both CVC, VCC, and CCV words, for example, *bil* (car), *ost* (cheese), and *tre* (tree). Ten words will be familiar from the reading material, and 10 words will be novel; the words are thus not being worked explicitly through the reading intervention.

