## Methodology

### Aims

This trial investigates whether non-verbal or minimally verbal students with intellectual disabilities, who require AAC, can acquire foundational reading skills through instructions in phonological awareness (sound blending and phoneme segmentation), letter-sound correspondence, shared reading, sight words, and decoding by working systematically and explicitly with the reading program “Lesing for alle” (“Reading for All”). The adapted reading material has been prepared and designed in line on the basis of the research of the evidence-based reading program Accessible Literacy Learning (ALL) [3].

The research questions are as follow:Is there a functional relationship between the use of “Lesing for alle” and increased accuracy of sound blending by students age 6–14 with intellectual disabilities who require AAC?Is there a functional relationship between the use of “Lesing for alle” and improved acquisition of letter-sound correspondence by students age 6–14 with intellectual disabilities who require AAC?Is there a functional relationship between the use of “Lesing for alle” and improved acquisition of phoneme segmentation by students age 6–14 with intellectual disabilities who require AAC?Is there a functional relationship between the use of “Lesing for alle” and improved acquisition of recognition of sight words by students age 6–14 with intellectual disabilities who require AAC?Is there a functional relationship between the use of “Lesing for alle” and improved acquisition of decoding by students age 6–14 with intellectual disabilities who require AAC?Is there a positive and strong correlation between increasing skills from 1–3 to 4–5? Meaning, is there a transfer from lower-level skills (phonological skills) to decoding skills?

As this trial is a multiple single-case design, there were no comparator interventions chosen.

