### Design

This study will be conducted with multiple single-case design with four multiple randomized baselines, where the shortest baseline has two assessments and the largest has five, and the intervention phase has 18 assessments across time. We have recruited 40 students with intellectual disabilities who require AAC.

To evaluate the effectiveness of the intervention effects in this study, the What Works Clearinghouse (WWC) single-case design technical documentation provides appropriate study analysis techniques [20]. Andzik and Chung [8] recommend that researchers follow these quality guidelines for single-case experimental studies to ensure internal validity of the study with reliable measures (Fig. 1).

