**Fig. 1 Fig1:**
[figure not shown]
Assessments to be administered. This trial protocol is in line with standard protocol items: Recommendations for Interventional Trials (SPIRIT) 2013. Standard Protocol Items: Recommendations for Interventional Trials (SPIRIT) figure with timeline for recruitment, assessments, and interventions. Black lines indicate “conducted every month,” and X indicate “only conducted three times across 18 months, i.e., month 1, 12, and 18.” A, B, C, and D indicate the four randomized groups and when they start the reading intervention

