### Intervention description

#### Recruitment

To recruit students, lectures were held at 12 schools, both ordinary schools, special schools, and schools with reinforced departments. The lectures were held in the period August to December 2022. The lectures emphasized informing about the reading program and the reading material “Reading for All” and about implementation and criteria for the reading intervention. Teachers, who had students within the criteria, registered themselves on an interest list, which the headteacher at the school passed on to the researcher. All the teachers were sent information letters and consent forms which they in turn sent to the parents, and all parents can contact the researchers by phone or email at any point in time during and after the trial. The teachers received their own consent forms. The principals at the respective schools collected all the consent forms and put them in sealed envelopes. They were then collected by the researcher and placed in a locked filing cabinet. The teachers who participate in the study will not be linked to the individual student, which help to strengthen the anonymity of the participants. The teachers and parents were asked to fill in the MacArthur-Bates Communicative Development Inventories (CDI) to document the individual student’s communicative competence. In February 2023, the teachers received training regarding the assessments and material. Baseline started in week 10 of March for all students.

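### At the listed test months the randomised baselines give no on/off contrast for sight words and decoding, and the stated number of test occasions does not add up

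*Protocol article*

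**What the plan says.** The Secondary outcomes section gives the schedule for sight words and decoding: "The time frame is as follows: two time points during baseline phase, two during intervention (months 1, 12, and 18". The Fig. 1 legend describes a set of assessments marked X as "only conducted three times across 18 months, i.e., month 1, 12, and 18". It does not name the tests, but the months match those in Secondary outcomes.

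The Design section states that "where the shortest baseline has two assessments and the largest has five". Recruitment adds: "Baseline started in week 10 of March for all students". The Fig. 1 legend explains that "A, B, C, and D indicate the four randomized groups and when they start the reading intervention". For the primary outcomes the schedule is monthly: "Primary outcomes will be assessed 18 times in equidistant time points, every month, across 18 months".

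In Aims, research questions 4 and 5 ask whether there is a functional relationship between the program and, respectively, recognition of sight words and "improved acquisition of decoding by students". The same section says that no comparator intervention was chosen. The Statistical analysis plans section names a GEE for the effect of the intervention after baseline and rules out additional analyses.

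**The concern.** With no comparator arm, the only control in this design is the staggered start: at some calendar months, randomly chosen students are already on the program while others are still in baseline. An outcome benefits from that control only if it is measured in those months. Sight words and decoding appear to be measured only before anyone starts and long after everyone has started.

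If so, the coefficient for phase on these two outcomes takes in everything else that changes over 11 to 17 months in schoolchildren whose ordinary teaching continues. A positive result would be reported as an answer to questions 4 and 5, although the randomisation contributed nothing to it. The mismatch in the count matters too, because it leaves unclear whether each student has one baseline score or two.

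**Working it through.** **Occasions.** By phase, the text gives 2 + 2 = 4. By month, it lists 1, 12 and 18, which is 3, as in the Fig. 1 legend. Of these only month 1 is in baseline, so the listed months supply one baseline score, not two.

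**Inputs for the phase check.**
- Common start in March 2023 (Recruitment).
- Baselines of 2 to 5 assessments (Design). The middle lengths, 3 and 4, are inferred; the result needs only the stated minimum and maximum.
- Monthly spacing (Primary outcomes).
- 40 students (Design).

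**Phase by month.** A group with baseline length b is on the program in month m when m > b, with exposure m − b.

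| Month | A (b = 2) | B (b = 3) | C (b = 4) | D (b = 5) |
|---|---|---|---|---|
| 1 | baseline | baseline | baseline | baseline |
| 3 | 1 | baseline | baseline | baseline |
| 4 | 2 | 1 | baseline | baseline |
| 5 | 3 | 2 | 1 | baseline |
| 12 | 10 | 9 | 8 | 7 |
| 18 | 16 | 15 | 14 | 13 |

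Groups are in different phases only in months 3, 4 and 5. At the listed months the number on the program is 0 of 40, then 40 of 40, then 40 of 40 (ignoring drop-out).

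**Estimability.** Take one effect per calendar month plus a phase indicator. At months 1, 12 and 18 the phase column equals the sum of the month-12 and month-18 columns: 4 parameters, rank 3, so the phase effect is not estimable. Adding a second baseline test changes little:
- at month 2 for everyone: 5 parameters, rank 4;
- at each group's last baseline month: 8 parameters, rank 7.

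Neither is estimable, because no calendar month then contains both phases. Monthly testing, as for the primary outcomes, gives 19 parameters and rank 19.

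**What randomised information remains.** At months 12 and 18 the groups differ in exposure by at most 10 − 7 = 16 − 13 = 3 months. If the gain per month on the program is assumed constant, the standard error is about 0.10 SD per month, or 3 × 0.10 = 0.30 SD for A against D. This assumes 10 students per group and borrows the intraclass correlation of 0.5 and autoregressive effect of 0.5 from the power section.

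**Does the month count start elsewhere?** Design gives the intervention phase 18 assessments, while Primary outcomes gives 18 in all, so the numbering is not fully fixed. Suppose months ran from each student's own start. For D, baseline would take March to July 2023 and 18 further months would run from August 2023 to January 2025. That is past both completion dates in Trial status (October and December 2024). Month 1 would then not be baseline at all, and the count in Secondary outcomes would still not fit.

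**The case against.** **The month effects are not the plan's own.** The article does not say that calendar month enters the GEE. That is true, and without it a phase coefficient can be computed, but it then absorbs all change over time. With a straight-line trend instead, the effect is estimable (standard error about 0.39 SD), but it rests on the line being straight and not on the randomisation.

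**Late, sparse testing has a rationale.** In the material, single-word decoding enters at Level 2, after eight Level 1 folders, and sight words at Level 3, after 8 + 13 = 21 folders, apart from brief introductory tasks at Level 0. A student needs 80% correct to leave a folder. This stands as a reason for the schedule, but it does not supply the missing control. It also answers a reader who might infer that one test around month 4 would repair the design. Groups A and B would then be only in their second and first month of the program, and few would have been taught these skills. The contrast would be estimable but could easily be near null for that reason alone.

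**The timing may be fixed elsewhere.** Fig. 1 is not shown, and each student has an individual follow-up plan. Either may settle the count. Neither removes the confounding if testing takes place at the stated months.

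**Stronger readings that the documents do not support.** A reader might infer that questions 4 and 5 yield no information at all. They do yield a describable before-after change and the small exposure difference above. A reader might set an assumed background drift against the effect size of 0.5 in the power section. That figure belongs to a calculation with alpha set for three primary outcomes, and the article gives no drift rate. A reader might also fault the autoregressive matrix for the unequal gaps between occasions. In a GEE a misspecified working correlation mainly costs efficiency, and with robust standard errors it does not bias the mean estimate.

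**Conclusion.** The concern holds in a limited form. The stated occasions contradict each other: four by phase, three by month, with one baseline score where two are promised. At the listed months, counted from the common March 2023 start, phase is fully confounded with calendar time for sight words and decoding, so the staggered baselines give no on/off contrast for these two outcomes. The functional relationship in questions 4 and 5 cannot be attributed to the program from the planned before-after comparison. The amount of bias is unknown, because the article gives nothing from which to estimate background change.

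The conclusion rests on calendar-month numbering and on testing only at the listed months. It does not touch sound blending, letter-sound correspondence or phoneme segmentation, which are tested monthly. Since two secondary outcomes are affected and rewording deals with it, this is a point that should be fixed; it does not threaten the trial's main result.

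**What to change.** - Reword research questions 4 and 5, and any conclusion on the secondary outcomes, as change over time without a controlled comparison.
- State one number and one timing of occasions, the same in Secondary outcomes and in the Fig. 1 legend, and say from what date months are counted. Where an occasion has already passed, give the timing actually used.
- If the second baseline occasion is kept, place it at each student's last baseline month. The two baseline scores would then be 1, 2, 3 or 4 months apart (2 − 1 to 5 − 1), so drift before the intervention can be described. This does not restore the controlled contrast, and the text should say so.

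The cost is wording and, at most, fixing the date of an occasion that the text already counts. The downside is a weaker claim for two secondary outcomes, one of which, decoding, is the closest to actual reading.

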
Emphasis will also be placed on working with additional activities such as flash cards and working on conceptual learning of the words they encounter in the reading program. All teachers get an overview of all the words that belong to the various levels in the reading material. It will be important to ensure basic comprehension skills on word level.

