During the first step, the teacher is modeling for the student what will be required of them in each task and the student is a passive observer. The only expectation of them is that they are paying attention to the teacher. The teachers must follow the various scripts in the various reading components. The first step in the task is for the teacher to name all the four symbols and say “I’m going to say a word, listen to the word.” The teacher says the target word (for example seal). “Ssseeeaaalll,” the teacher says the word gradually faster, “sseeaall,” and finally say it normally, “seal.” Then, the teacher says “now I look at the symbols” and choose the symbol for “ssseeeaaalll.” The teacher points to the symbol for seal and at the same time says “ssseeeaaall” is a seal.”

During the second step, guided practice, the student is expected to be active in the lesson and is encouraged to point to the target item as well. In this step, the students get support to complete the tasks correctly together with the teacher. The teacher starts by saying “let’s do the task together.” It is the same script as in the modeling phase, but the teacher encourages the student to do it together.

During the final step, independent practice, students must perform independently. Teacher emphasizes and says “now it’s your turn, tap the glue icon.” If the student points to the correct symbol, the teacher says “good, g-llluuueee is glue.” The teacher points and confirms that the student has chosen the correct symbol. If the student answers incorrectly, the teacher corrects immediately and says “You pointed to xx (wrong answer), we have to find glue.”*Level 1*. Eight folders (with about 120 tasks in sound blending, letter-sound correspondence, and shared reading in each folder)*Level 2*. Thirteen folders (with about 120 tasks in sound blending, letter-sound correspondence, phoneme segmentation, single-word decoding, and shared reading in each folder)*Level 3*. Ten folders (with about 150 tasks in sound blending, letter-sound correspondence, phoneme segmentation, sight words, single-word decoding, advanced word decoding (for example, words with multiple consonant accumulations), not phonetic word pictures, recognition of high-frequency words, and shared reading in each folder)

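### The single 0–20 decoding score pools ten familiar words with ten novel ones, so a rise in it need not show decoding; the novel words should be scored separately

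*Protocol article*

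**What the plan says.** Under Secondary outcomes the article gives the range and source of the measure: "Decoding [score ranging from 0 to 20] measured by adapted tests in line with the reading material". The test has 20 items, and the response format is the same for all of them: "The students must discriminate between four symbols, where one symbol represents the target word". The items are of two kinds: "Ten words will be familiar from the reading material, and 10 words will be novel". Of the novel words it adds that "the words are thus not being worked explicitly through the reading intervention". The skill the test is meant to capture is sequential: recognise the letters, attach sounds, hold them in memory, "blend the sounds to determine the word", and then find the symbol. No separate score for familiar and novel words is stated.

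In the list of program components under The reading material, recognising a word without sounding it out is a component of its own (sight words), distinct from single-word decoding. The same section says of the words met in the program: "Emphasis will also be placed on working with additional activities such as flash cards".

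Under Aims, question 5 asks whether the program improves decoding. Question 6 asks whether gains in the three phonological skills correlate with gains in sight words and decoding, and glosses this as follows: "Meaning, is there a transfer from lower-level skills (phonological skills) to decoding skills".

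Under Design of the material, single-word decoding is among the Level 0 tasks. It appears again at Level 2 ("Thirteen folders (with about 120 tasks in sound blending, letter-sound correspondence, phoneme segmentation, single-word decoding, and shared reading in each folder") and at Level 3.

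**The concern.** Half of the decoding items can in principle be answered by a skill that the article separates from decoding. A student who has come to know some familiar words by their overall look can pick the right symbol without using letter-sound links or blending. Only the novel words distinguish the two explanations, and the stated score adds them to the familiar ones.

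The stake is the interpretation of question 5. The abstract's discussion says the trial should go beyond teaching sight words alone. A decoding score that sight recognition can raise does not show whether it has done so. Question 6 uses the same score as part of its outcome side, so the problem carries over there in weaker form.

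**Working it through.** **Inputs from the article.** Twenty items, 10 familiar and 10 novel, and 10 + 10 = 20 reproduces the stated range. Four options per item give a guessing probability of 1/4 = 0.25. Students who can already decode single words and syllables are excluded (Exclusion criteria), so a starting level near chance is a reasonable assumption.

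**Assumptions.** k familiar words are memorised and always answered correctly. All other items are guessed independently at 0.25, and nothing is decoded. The article does not allow k to be estimated, so a range is shown.

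**Expected scores.**
- Total: E = k + (20 − k) × 0.25.
- Novel words: 10 × 0.25 = 2.5, whatever k is.

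As a benchmark for a score above chance (mine, not the article's), take 9 or more of 20, which a pure guesser reaches with probability 0.041. For the ten novel words, take 6 or more of 10, with probability 0.020.

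| k | Expected total | Rise over chance | P(total ≥ 9) | Expected novel score | P(novel ≥ 6) |
|---|---|---|---|---|---|
| 0 | 0 + 20 × 0.25 = 5.0 | 0 | 0.041 | 2.5 | 0.020 |
| 3 | 3 + 17 × 0.25 = 7.25 | 2.25 | 0.23 | 2.5 | 0.020 |
| 5 | 5 + 15 × 0.25 = 8.75 | 3.75 | 0.54 | 2.5 | 0.020 |
| 8 | 8 + 12 × 0.25 = 11.0 | 6.0 | 0.97 | 2.5 | 0.020 |
| 10 | 10 + 10 × 0.25 = 12.5 | 7.5 | 1.00 | 2.5 | 0.020 |

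The upper limit of the rise is 7.5/20 = 37.5% of the scale.

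**Can the total separate the two explanations?** A student who truly decodes half of all the words and guesses the rest has a per-item success probability of 0.5 + 0.5 × 0.25 = 0.625. The expected total is 20 × 0.625 = 12.5, the same as for the full memoriser. The expected novel score is 10 × 0.625 = 6.25, against 2.5. The total does not distinguish them on average; the novel subscore does.

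**Where the total does inform.** A full memoriser needs t − 10 correct guesses among the ten novel words to reach a total of t. The probabilities are 0.078 for 15 or more, 0.020 for 16 or more and 0.0035 for 17 or more. They are smaller still for k below 10. Very high totals therefore do point to novel-word decoding.

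**Question 6.** The article defines transfer as running from phonological skills to decoding, assessed by a correlation of gains. Familiar-word recognition enters the decoding gain. If it is unrelated to phonological gains, it acts as noise and weakens the correlation. If both grow with time spent in the program, it strengthens the correlation without any transfer. Decoding is also taught directly at Levels 0, 2 and 3, so gains in both sets of skills can share a cause even with a clean decoding score.

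**The case against.** **The full rise to 12.5 is an extreme case.** This stands. It needs all ten familiar words to be memorised perfectly. Nothing in the article says that the ten test words are on flash cards, or that each is practised in print; the material's squares may hold a symbol, a letter or a word. That is why a range is given.

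**Reading familiar words is a fair part of question 5.** This stands in part. It is a worthwhile result, but the article describes the test as measuring blending from letters and sounds, and familiar items alone cannot show that.

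**The split may be planned elsewhere.** The authors deliberately built in a novel half, and a separate analysis plan may use it. The statement under Statistical analysis plans that no additional analyses are planned gives subgroup and adjusted analyses as its examples, so it does not clearly rule out subscores. The point therefore rests only on the outcome as the article defines it, a single 0–20 score.

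**Question 6.** A reader might infer that pooling leaves the transfer question untested, or that questions 5 and 6 could both come out positive with no student decoding. The documents do not support this for question 6. Transfer there does not mean generalisation from familiar to novel words, and sight words are on its outcome side by design. A false positive would need memorisation to track phonological gains, which has not been shown.

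**Conclusion.** The concern holds as a weakness in how a secondary outcome is defined. Recognising familiar words can lift the expected total from 5 to between 7.25 (three words) and 12.5 (all ten) with no decoding, while the novel-word score stays at its chance value of 2.5 of 10. This rests on guessing at 0.25, memorised words always being correct, and a k that the article leaves unknown.

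Question 5 is hit most directly: a moderate rise in the total does not by itself answer it. For question 6 the effect is contamination of the decoding side and a weaker reading as transfer, no more than that. The total is not uninformative, since 16 or more would be unlikely from recognition alone. The point is worth acting on because the remedy is cheap.

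**What to change.** - Define two decoding subscores of 0–10 each, one for familiar and one for novel words.
- Name the novel-word subscore as the decoding measure for question 5 and for the decoding part of question 6. Sight words stay in question 6 as they are.
- Report the familiar-word subscore as reading of taught words, and keep the 0–20 total as descriptive.
- Report the question 6 result as an association between gains, not as evidence of transfer.

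No new data are needed. Under Assessment of the outcomes, the teacher registers the option chosen and whether it is correct, all test sessions are filmed, and sampled films are rated item by item. The cost is precision: with independent items of equal difficulty, the standard error of a proportion correct is √(p(1 − p)/n), so moving from 20 to 10 items multiplies it by √(20/10) = 1.41.
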